#### Secondary outcome

##### Depressive symptoms

Depressive symptoms are monitored by means of the Centre for Epidemiologic Studies Depression Scale CES-D. This instrument is designed specifically for the screening of depression but has also been found to be a satisfactory screener for anxiety disorders [42]. It consists of 20 items and its total score has a range between 0 and 60. Scores > 15 indicate clinical significant levels of depressive and anxiety symptoms. The CES/D is also used for follow up purposes.

##### Anxiety symptoms

For follow up measurements of symptoms of anxiety the seven anxiety items of the Hospital Anxiety and Depression scale (HADS-A) [43] will be used in addition to the CES-D. The aim is to optimise the sensitivity and specificity of the CES-D for subthreshold anxiety.

##### Quality of life

Quality of life will be measured using the EuroQol. Using the British and the Dutch tariff [44,45], the 5 dimensions of the EuroQol will be valued to obtain utilities. Subsequently, Quality Adjusted Life Years (QALYs) will be calculated by multiplying the utilities with the amount of time a resident spent in this health state.

##### Health care utilization

A cost-effectiveness analysis will be performed from a societal perspective. Direct health care costs (e.g. visit to GP, specialist and use of medicines) and direct non-healthcare costs (self medication) are assessed with an interview based on the Trimbos/iMTA questionnaire for Costs associated with Psychiatric Illness (TiC-P). This questionnaire is developed by the Trimbos Institute Utrecht in combination with the institute for Medical Technology Assessment Rotterdam. Since all patients were living in a home for the elderly lost productivity costs and costs of informal and formal care are not relevant in this study. Resource use was measured using an interview that was based on the TiC-P. All direct costs are considered because it is difficult to determine which costs are associated with the depression and which are not. Resource use is valued using Dutch standard costs [46]. Medication costs will be valued using prices of the Royal Dutch Society for Pharmacy [47].

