**Methods/Design:**

This protocol describes a randomised trial on the feasibility and (cost) effectiveness of a stepped-care programme for prevention of depressive and anxiety disorders in homes for the elderly. The main outcome measure is the incidence of depressive and anxiety disorder in one year with a two years follow up. Secondary outcomes are symptoms of depression and anxiety, quality of life, direct health care costs and satisfaction with treatment.

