Although caregivers in the homes recognize the impact of the problem as described earlier, symptoms of depression and anxiety are rarely identified and labelled as such [15,16]. A substantial part of residents of homes for the elderly suffers from physical co-morbidity. Symptoms of depression and anxiety disorder like apathy and weariness may also be ascribed to physical illnesses [17]. This makes that symptoms of anxiety and depression are often interpreted only as consequences of decline rather than problems that require intervention. Physical illness in the elderly is most of the time progressive and hard to cure. Depressive and anxiety disorders, however, have more optimistic possibilities for prevention and treatment [14,18,19]. Moreover, as the population is ageing rapidly and the policy in the Netherlands is to facilitate independent living as much as possible, the level of psychological and physical frailty in homes for the elderly has been increasing rapidly. At the same time, medical care is also changing: General Practitioners (GPs), who are responsible for medical care in the residential homes in the Netherlands, have for instance halved the number of house visits since 1987 [20]. In addition, most homes suffer from staff deficits, in which cases the quality of care is threatened [21]. Therefore, efficient use of the available, scarce resources, as supplied by this stepped care protocol, is of great importance.

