### Interventions

#### Stepped-care protocol

Our intervention protocol is based on the protocol of The Prevention of Anxiety and Depression in Late Life consortium (PADLL, in which several Dutch universities and the national mental health institute collaborate) [22]. This consortium designed a generic stepped-care intervention protocol to be tested across different health care settings, different groups of elderly persons and different forms of prevention (prevention of episodes vs. relapse prevention). For use in homes for the elderly, we selected the interventions that seemed to be most suitable for this frail and isolated population. In organizing this stepped-care approach, evidence-based guidelines are used as far as possible. Staff in the homes for the elderly and mental health nurses will be contracted to cooperate in the stepped-care protocol. One caregiver will coordinate the care. Necessary training will be provided. When residents show continuously elevated CES-D scores, GPs of the residents will be involved.

The protocol contains the following steps (see Figure 1):

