##### Step 2: biblio-therapy and a signal to the GP

Participants, who still have symptoms of depression and anxiety after 3 months of watchful waiting, as measured with the CES-D, are informed about the possibility of learning to cope with these symptoms by a self-help course for coping with depression and anxiety with an accent on activity scheduling. Self administered treatments for depression and anxiety have proven to be successful in clinical practice and for older adults [19,34-39]. Staff will be trained to accompany and stimulate the residents while working through the course in their own tempo. At the same time, GPs will be involved by informing them about the persisting symptoms. After a period of three months the third measurement will take place.

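### The economic evaluation is called societal, but formal and informal care are ruled out for a reason that does not hold, so the costs counted do not match the stated perspective

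*Protocol article*

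**What the plan says.** The Health care utilization section of the protocol article opens with the perspective: "A cost-effectiveness analysis will be performed from a societal perspective". It names the costs to be collected by an interview based on the TiC-P: "Direct health care costs (e.g. visit to GP, specialist and use of medicines) and direct non-healthcare costs (self medication").

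It then excludes three categories because the participants live in a home for the elderly: "lost productivity costs and costs of informal and formal care are not relevant in this study". Shortly afterwards it says: "All direct costs are considered because it is difficult to determine which costs are associated with the depression and which are not".

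The abstract's list of outcomes is shorter: "Secondary outcomes are symptoms of depression and anxiety, quality of life, direct health care costs and satisfaction with treatment".

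On delivery of the programme, the Stepped-care protocol section says: "Staff in the homes for the elderly and mental health nurses will be contracted to cooperate in the stepped-care protocol". It adds that one caregiver coordinates the care and that training is given. For step 2: "Staff will be trained to accompany and stimulate the residents while working through the course in their own tempo". Step 3 is given by a mental health nurse who is trained and supervised for it. The Usual care section says that nurses and care workers in the home provide the generic daily care.

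The Analysis section forms both ratios by dividing the between-arm difference in total costs by the difference in clinical effect or in QALYs.

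**The concern.** A societal analysis counts resource use whoever pays for it. Removing formal and informal care takes out two categories that such an analysis would normally contain, and formal care is probably the largest of all for people in residential care. The exclusion is a stated decision with a stated reason, so it is not a detail that was merely shortened for the article.

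The reason is sound for lost productivity in this population, and that part is not contested. It does not carry over to formal care. Living in a home means that formal care is always present. It does not mean that the amount is the same in both arms.

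The Background makes staff time a central resource: "In addition, most homes suffer from staff deficits, in which cases the quality of care is threatened". It presents stepped care as an efficient use of scarce resources and says that these disorders go with disability and service use. If the programme works as intended, time spent by home staff is one of the places where a difference would appear. A ratio that leaves this out cannot support a societal claim about cost-effectiveness, and cost-effectiveness is one of the trial's declared aims.

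**Working it through.** The plan gives no unit cost, staff hours or expected cost difference, so there is no figure of its own to reproduce. The check is mainly a comparison of statements.

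**1. Label against content.** The label is societal. The costs named are GP and specialist visits, medicines and self medication. Formal and informal care are explicitly out. The statement that all direct costs are considered cannot stand beside this, because formal care is a direct cost.

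**2. The reason given.** The exclusion would do no harm if formal and informal care were equal between arms. Residence in a home does not secure that:

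- Randomisation is by resident in blocks within each home, so the arms share each home's staffing level at the start. Staff time per resident after randomisation can still diverge if one arm develops fewer disorders.
- Home staff support step 2 and are contracted for the programme. That time arises in the intervention arm.
- Residence does not rule out informal help from relatives.

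**3. What an omission does to the ratio (illustration).** Let D be any programme delivery cost left uncounted per intervention resident. Let S be the formal and informal care saved per intervention resident relative to control, also uncounted. Then:

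- true cost difference = recorded difference + D − S
- amount by which the ratio is understated = (D − S) / difference in incidence

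The Sample size section gives 35% within two years under usual care and a target of 20%, so the difference is 0.35 − 0.20 = 0.15. I take both figures at the same two-year horizon. D and S are assumed, in arbitrary currency units:

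| D | S | D − S | Effect on cost per disorder prevented |
|---|---|---|---|
| 50 | 0 | 50 | 50 / 0.15 = 333 too low |
| 100 | 0 | 100 | 100 / 0.15 = 667 too low |
| 400 | 0 | 400 | 400 / 0.15 = 2,667 too low |
| 100 | 100 | 0 | none |
| 100 | 200 | −100 | 667 too high |
| 50 | 400 | −350 | 2,333 too high |

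Too low favours stepped care; too high works against it. The sign turns on whether D exceeds S, and the document gives neither. No expected QALY difference is stated, so the same step cannot be done for the cost-utility ratio.

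**The case against.** The strongest defence is that formal care here means routine residential care, since it stands beside lost productivity and informal care and is excluded because of where participants live. On that reading the cost of the programme is a separate matter. Several points support this. The items named for the interview are introduced as examples, so the list is not closed. Training and supervision hours would not come from a resident interview in any case. Staff and nurses are contracted, the text says that all direct costs are considered, and the ratios use total costs. How intervention costs are built up is also something a condensed article may leave to the full plan.

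This stands as far as it goes. A reader might infer that the plan hides the staff time spent on delivery and so biases the result towards stepped care. The document does not support that: nowhere does it say that delivery, training or supervision goes uncosted, and even if it did, omitted care savings would pull the other way. A reader might also take the abstract's cost outcome as yet another perspective. It names an outcome in shortened form and no perspective.

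The defence does not rescue the exclusion itself. Even if formal care means only routine residential care, that care is still a societal cost whose volume may differ by arm, and the reason given does not show otherwise. The same holds for informal care.

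**Conclusion.** The point holds as a mismatch between the stated perspective and the costs counted, resting on a justification that fails for formal and informal care. That much follows from the Health care utilization section itself and needs no outside figure.

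Two further matters remain open. Whether programme staff time falls under the exclusion is not stated; if it does, intervention cost is understated. The net direction of any bias is unknown, because uncounted delivery time and uncounted care savings act in opposite directions. The scale of about 667 per disorder prevented for each 100 units of net omitted cost depends on the planned 35% versus 20% and on assumed costs. It shows sensitivity and does not estimate the error.

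The issue concerns the economic evaluation only and leaves the primary comparison of incidence untouched. It should be corrected, because it decides what the cost-effectiveness and cost-utility ratios may be said to show.

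**What to change.** Choose one of two options.

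- **(a) Keep the societal perspective.** Withdraw the exclusion of formal and informal care and measure both: formal care from the homes' records or from added interview items, and informal care from added interview items. Home records may serve better than recall for formal care in this frail group. The exclusion of lost productivity can stay.
- **(b) Narrow the perspective.** Delete the justification that calls formal and informal care irrelevant. Describe the analysis by what it counts, namely direct health care costs plus self medication. A pure health-care label would not fit, because self medication is classed as a non-healthcare cost. State that formal and informal care are not measured, and limit the conclusion accordingly.

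Under either option, say explicitly that home-staff and nurse time, coordination, training and supervision are included as intervention-arm costs within total costs. Describe the scope of costs consistently wherever the economic results are reported.

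The cost is modest. Both options need a log of programme hours, and (b) otherwise needs only rewording. Option (a) adds some data collection from home records or at interviews already planned.

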##### Patient satisfaction

To measure satisfaction with the treatment, the "GGZ thermometer, developed by the national mental health institute (Trimbos), is chosen. The instrument focuses on the appreciation of treatment explanation, the caring staff and the result of the interventions.

#### Effect modifiers

We assess the following potential effect modifiers on the level of de residents: presence of chronic illnesses and handicaps [48], social support [49], loneliness [50], personality (mastery) [51] and socio demographic characteristics, such as age, gender, level of education and marital status.

Table 2 displays the outcome parameters and instruments and additionally used questionnaires

### Sample size

Based on the prospective data of the Longitudinal Ageing Study Amsterdam (LASA) we conservatively estimate the incidence rate of depressive and/or anxiety disorder of elderly with symptoms of anxiety and/or depression within two years at 35% [33,52]. Our aim is to reduce incidence of full blown anxiety and depression disorders in the prevention group to 20%. To be able to detect this reduction (alpha = 0.5 and power = 0.80) 134 completers are needed, 67 in both conditions [53]. In the population of elderly persons in residential homes, substantial drop out (attrition) is expected because of illness and mortality. This is estimated at 20%, so therefore we need 172 participants. We know from previous projects that two thirds of subjects complete the CES-D, and we assume 40% will score 16 or more [22]. We estimate that 20% of these subjects already have a depressive and/or anxiety disorder and therefore will be excluded. With 80% consenting for randomization, we conservatively need to screen 1200 residents to find 86 residents per arm.

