### Randomization

At least 172 residents will be included; 86 will start in the intervention group who follow the stepped care protocol. The other 86 will receive care as usual. Subjects are randomized at the patient level per home in computer generated blocks of four by an independent statistician, simultaneously with the inclusion in the study. Blocking is used to ensure that comparison groups are of approximately the same size per home.

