### Analysis

To examine differences on the primary outcome, survival analysis will be used. The secondary outcome measures are analysed using random coefficient analyses. The analyses will be performed according to the "intention to treat" principle. Additionally, data will be analyzed according to the per protocol principle. Differences in total costs between both groups are assessed and confidence intervals are estimated using bias-corrected and accelerated bootstrapping with 2000 replications [54]. Cost-effectiveness and cost-utility ratios will be calculated by dividing the difference in total costs between the intervention and usual care group by the difference in the clinical effect measures and QALYs between the treatment groups. Uncertainty around the cost-effectiveness and cost-utility ratios will calculated using the bias-corrected percentile bootstrapping method (5000 replications) [55]. The bootstrapped cost-effect pairs were plotted on a cost-effectiveness plane.

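### With 67 completers per arm, power for 35% versus 20% is about 50%, not the stated 80%; 80% needs about 138 completers per arm

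*Protocol article*

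**What the plan says.** All the inputs except sidedness are in the protocol article, under Sample size. Two-year incidence without the programme is put at 35% and the target with it at 20%. Then: "To be able to detect this reduction (alpha = 0.5 and power = 0.80) 134 completers are needed, 67 in both conditions". On attrition from illness and death: "This is estimated at 20%, so therefore we need 172 participants". The Randomization section carries the result forward: "At least 172 residents will be included; 86 will start in the intervention group who follow the stepped care protocol", with the other 86 in usual care. The Analysis section states "To examine differences on the primary outcome, survival analysis will be used", without further detail on the test behind the sample size. Neither the formula nor the sidedness is given.

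**The concern.** A 15-point difference between 35% and 20% ordinarily needs well over 100 per arm at conventional error rates, so 67 per arm looked too small by about half. The printed alpha of 0.5 is implausible in itself, and the attrition step does not follow from the completers figure either: 134/0.8 = 167.5, not 172.

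The calculation sets the recruitment target for the primary aim, prevention of disorder onset. If power is really near 50%, a true reduction of the size the trial was designed around is about as likely to be missed as found, while readers are told that the risk of missing it is 20%.

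**Working it through.** **Inputs** (Sample size section): p1 = 0.35, p2 = 0.20, power 0.80, 1:1 allocation, 67 completers per arm, 20% attrition. Assumed: alpha 0.05, two-sided. One-sided tests and the literal 0.5 are also tried.

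**1. Trying to reproduce 67 per arm.** Pooled two-proportion formula, with mean proportion 0.275:

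n per arm = [z_alpha × √(2 × 0.275 × 0.725) + 0.8416 × √(0.35 × 0.65 + 0.20 × 0.80)]² / 0.15²

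The two square roots are 0.6315 and 0.6225. With z_alpha = 1.96:

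n = (1.2377 + 0.5239)² / 0.0225 = 137.9, so 138 per arm.

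| Variant | Completers per arm for 80% power |
|---|---|
| Two-sided 0.05, pooled | 138 |
| Two-sided 0.05, unpooled | 135.2 |
| Two-sided 0.05, arcsine | 136.8 |
| Two-sided 0.05, continuity-corrected | 151 |
| One-sided 0.05, pooled | 109 |
| One-sided 0.10, pooled | 79 |
| Two-sided 0.5 (literal), pooled | 41 |
| One-sided 0.5 (literal), pooled | 13 |

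None gives 67.

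**2. Power that 67 per arm does give.**

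Power = Φ{[0.15 × √67 − 1.96 × 0.6315] / 0.6225} = Φ{(1.2278 − 1.2377) / 0.6225} = Φ(−0.016) = 49.4%

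Exact enumeration of the chi-square test gives 49.6%, arcsine 50.0%, Fisher's exact test 42.4%. One-sided 0.05 gives 61.9%, one-sided 0.10 gives 74.9%, and literal two-sided 0.5 gives 90.1%.

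**3. Power on the planned 172.** 172 × 0.8 = 137.6 completers, about 69 per arm: power 50.5%. If all 86 per arm were analysed: 59.7%.

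**4. Survival analysis.** Under proportional hazards, HR = ln 0.80 / ln 0.65 = 0.518 and ln HR = −0.658. Schoenfeld's formula gives 4 × (1.96 + 0.8416)² / 0.658² = 72.6, so 73 events. Expected events are n per arm × (0.35 + 0.20):

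| Basis | Events | Power, two-sided 0.05 |
|---|---|---|
| 67 per arm | 36.9 | 51% |
| 69 per arm | 38.0 | 53% |
| 86 per arm, no dropout | 47.3 | 62% |

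**5. Detectable effect.** With 69 completers per arm and p1 = 0.35, power reaches 80% at p2 of about 0.146. The relative reduction is (0.35 − 0.146)/0.35 = 58%, against the planned 0.15/0.35 = 43%.

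**6. Number for 80% power.** 2 × 138 / 0.8 = 345 randomised, or 172 to 173 per arm.

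**Possible origin.** The stated total of 134 lies within about 3% of the per-arm requirement (135 to 138), and 138/0.8 = 172.5 is close to the stated 172. A per-arm number may have been taken as the total. This is an inference, because the formula is not shown, and nothing above depends on it.

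**The case against.** The best counter-argument is that 49% is the low end of a range. The primary analysis is a survival analysis by intention to treat, with diagnostic interviews at 3, 6, 9, 12 and 24 months, so residents who leave contribute follow-up until they do. Sidedness is not stated, so two-sided is an assumption. Both points stand as far as they go. They lift power to at most about 62%, either with no dropout at all or with a one-sided test, and neither reaches 80%.

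It can also be said that 172 is a minimum and that the 1200 to be screened are described as a conservative number. That is correct. On the section's own rates, 1200 × 2/3 × 0.4 × 0.8 × 0.8 = 205 could be randomised; after 20% attrition that is 82 per arm and about 58% power. The margin helps but does not close the gap.

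Finally, the printed alpha is plainly a misprint and should carry no weight of its own. That is accepted: the conclusion is drawn with alpha read as 0.05. Nor is the figure something left to an analysis plan or lost in condensing the article, since it is printed with its inputs and recruitment is set from it.

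**Conclusion.** The concern holds. Under the protocol's own incidences, 67 completers per arm give 49% power at two-sided 0.05, and the 69 per arm implied by 172 randomised give about 50%. The stated 80% needs about 138 completers per arm, roughly twice the plan. This rests on reading alpha as 0.05 and the test as two-sided. Relaxing the second assumption, or assuming no attrition in the log-rank calculation, raises power only to about 62%. Reading alpha literally as 0.5 puts power near 90%, so the statement is wrong on that reading too. Nothing elsewhere in the protocol lowers the required number.

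**What to change.** In the Sample size section, correct alpha to 0.05, two-sided, and replace the power statement with wording such as:

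> With 172 residents randomised and 20% attrition, about 138 will complete (69 per arm). At two-sided alpha 0.05 this gives about 50% power to detect 35% versus 20%. The effect detectable with 80% power is 35% versus about 14.6%. Power of 80% for 35% versus 20% would need about 138 completers per arm, that is, about 345 residents randomised in total.

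This also brings the completers figure into line with the 172 in the Randomization section.

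The cost is a rewording and a less favourable power figure; no extra residents are needed. Should the sponsor prefer to keep 80% power for the original target, the cost is about twice the recruitment. On the section's own rates (2/3 × 0.4 × 0.8 × 0.8 = 0.171 randomised per resident screened), 345 randomised would mean screening about 345/0.1707 ≈ 2,020 residents rather than 1200.

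### The 67 completers per arm give about 49% power for 35% versus 20%, not the stated 80%; about 138 per arm are required

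*Protocol article*

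**What the plan says.** The sample size section of the protocol article gives all the design inputs. The incidence without the programme is put at 35% over two years ("within two years at 35"), and the aim is to "reduce incidence of full blown anxiety and depression disorders in the prevention group to 20" percent. The error rates are "alpha = 0.5 and power = 0.80". The result is that "134 completers are needed, 67 in both conditions". Attrition is then added: "This is estimated at 20%, so therefore we need 172 participants". The randomization section repeats the total and splits it equally: "At least 172 residents will be included; 86 will start in the intervention group who follow the stepped care protocol", with another 86 under usual care. The 134 is therefore used throughout as the number for the whole trial. For the analysis of the primary outcome, the analysis section states: "To examine differences on the primary outcome, survival analysis will be used".

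**The concern.** A difference of 15 percentage points between 35% and 20% normally needs well over 100 people per arm at the conventional 5% level and 80% power, so 67 per arm looked too small by about half. This is the only justification given for the size of the trial, and it concerns the primary outcome. If the figure is wrong, the trial would miss the effect it was designed to find about as often as it would detect it. A reader who trusts the stated 80% could then give a non-significant result more weight against stepped care than it can bear. The point is separate from the misprinted alpha: changing 0.5 to 0.05 leaves the power claim uncorrected.

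**Working it through.** **Inputs from the protocol article.** Control incidence 0.35, intervention incidence 0.20, difference 0.15, mean 0.275; power 0.80; 67 completers and 86 randomised per arm; attrition 20%.

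**Assumptions.** Alpha is read as 0.05 because the printed 0.5 cannot be meant. The test is taken as two-sided. Both are varied below.

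**Attempt to reproduce the plan's figure.** Two proportions with pooled variance under the null, per arm:

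n = [1.960 × √(2 × 0.275 × 0.725) + 0.842 × √(0.35 × 0.65 + 0.20 × 0.80)]² / 0.15²

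The roots are √0.39875 = 0.6315 and √0.3875 = 0.6225, so n = (1.238 + 0.524)² / 0.0225 = 137.9. That is 138 per arm or 276 in total, against the stated 67 and 134.

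**Other ways of computing the requirement (80% power)**

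| Method | Requirement |
|---|---|
| Two-sided 5%, unpooled variance | 136 per arm (135.2) |
| Two-sided 5%, arcsine | 137 per arm |
| Two-sided 5%, continuity correction | 151 per arm |
| One-sided 5%, pooled | 109 per arm |
| One-sided 10%, pooled | 79 per arm |
| Alpha 0.5 as printed, two-sided | 41 per arm |

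None of these gives 67.

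**Power with 67 per arm.** z = (0.15 × √67 − 1.238) / 0.6225 = (1.228 − 1.238) / 0.6225 = −0.016, so power is 49.4%. Exact enumeration of the chi-square test gives 49.6% and the arcsine formula 50.0%. One-sided at 5% it is 61.9%. At a literal two-sided alpha of 0.5 it would be 90%, so the misprint does not explain the figure. For 67 per arm to have 80% power, the two-sided alpha would have to be about 0.265.

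**Survival analysis.** Under proportional hazards, HR = ln(0.80) / ln(0.65) = 0.518.
- Schoenfeld's formula needs 4 × (1.960 + 0.842)² / (ln 0.518)², about 73 events. Freedman's needs 78.
- Expected events with 67 per arm: 67 × (0.35 + 0.20) = 36.9, giving 51% power.
- With 86 per arm and no loss: 86 × 0.55 = 47.3 events, giving 62% power. The corresponding figure for two proportions is 60%.

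**What 67 per arm can detect.** At two-sided 5%, 80% power is reached for a fall from 35% to about 14.3%. That is a relative reduction of (35 − 14.3) / 35 = 59%. The planned fall to 20% is a relative reduction of 15 / 35 = 43%, and the background section describes reductions of up to roughly 30% in earlier prevention studies.

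**Attrition step.** 134 / 0.8 = 167.5, which rounds up to 168 and not 172. By contrast 138 / 0.8 = 172.5. For 276 completers, 276 / 0.8 = 345 would have to be randomised.

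**The case against.** The strongest reply accepts the arithmetic but questions the interpretation.

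- **The explanation is a guess.** The article never calls 134 a per-arm number, and the standard formulas give 136 to 138. With 134 per arm the power would be 78.8%, close to 80% but not equal to it. The 172 could be a plain slip: 38 / 172 is 22% attrition instead of 20%. The source cited for the calculation is not available here. This stands: the mix-up of per-arm and total is a likely explanation, not a proven one. The finding does not depend on it.
- **49% is the low end.** It counts completers only, in a comparison of proportions at a two-sided level that the article does not state. In a survival analysis by intention to treat, residents who drop out contribute follow-up until they are censored. This stands in part: two-sided power would lie between about 51% and 62%. The 62% assumes no loss at all, whereas the plan expects 20%. All of these values are well below 80%.
- **Whether to enrol more is for the investigators.** The randomization section gives 172 as a minimum, so a larger trial is not excluded. This also stands, and the correction to the text leaves that decision open.

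**Conclusion.** The power statement is wrong as written. For 35% versus 20% at a two-sided 5% level, 80% power needs about 138 completers per arm, roughly twice the 67 planned; with 67 per arm the power is about 49%. The main figures assume that alpha is 0.05 and the test two-sided, but the conclusion does not depend on either choice: one-sided testing reaches only 62%, and the printed alpha of 0.5 does not lead to 67 per arm. The planned survival analysis does not close the gap. No unseen analysis plan could make these inputs yield 80% with 67 per arm.

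**What to change.** Rewrite the calculation in the sample size section.

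- State alpha as 0.05 and the test as two-sided, if that is what was intended.
- Give the requirement for 35% versus 20% at 80% power as about 138 completers per arm (276 in total).
- State that with 67 completers per arm the power for this difference is about 49%, or about 51% for the log-rank test, and that 80% power applies only to a fall to about 14%.
- Make the attrition step agree with the completer number it starts from.

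As a secondary matter, the primary result is best reported as an estimate with its confidence interval, since a non-significant result at this size would say little against a preventive effect.

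The cost is one reworded paragraph and a less favourable power figure. The correction itself needs no extra enrolment. Should the investigators prefer to keep the 80%, about 345 would have to be randomised. The article's own yield per resident screened is 2/3 × 0.40 × 0.80 × 0.80 = 0.171, so that would mean screening about 345 / 0.1707 ≈ 2,020 residents instead of 1,200.
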